#### Exclusion criteria

Exclusion criteria for participants in this study will be: (1) previous first MTPJ surgery, (2) currently pregnant, (3) significant first MTPJ deformity including hallux valgus (defined as a score of 2 or 3 using the Manchester scale [27, 28]), (4) the presence of one or more conditions within the foot or ankle that could confound pain and functional assessments of the first MTPJ such as forefoot pain that is not first MTPJ OA, (5) the presence of any systemic inflammatory condition such as gout or rheumatoid arthritis, (6) any medical condition that, in the opinion of the investigators, makes the participant unsuitable for inclusion (e.g. clinically important pain in the musculoskeletal system other than the first MTPJ), (7) an inability to speak and read English, (8) cognitive impairment, (9) intra-articular injections (such as corticosteroids) to the first MTPJ in the previous 3 months, (10) unwilling to discontinue use of any foot orthotic devices if currently wearing them, (11) currently wearing shoe-stiffening inserts and (12) regularly wear shoes that are not able to accommodate the shoe-stiffening inserts.

### Baseline assessment

#### Participant characteristics, major medical conditions, health status and anthropometrics

Participant characteristics (such as age, sex, weight, height, education and income level), major medical conditions and number of medications will be obtained via a structured questionnaire. Health status will be measured using the Short-Form-12 (SF-12®) Version 2.0 and the EuroQol 5D-5L™ (EQ-5D-5L™) questionnaires. Height and weight will be measured using a stadiometer and digital scales and Body Mass Index will be calculated as weight (kg)/height (m^2^). Static foot posture will be assessed using the Foot Posture Index [29]. First MTPJ dorsiflexion range of motion will be measured using a reliable goniometric technique [26]. Footwear will also be assessed using selected items from the Footwear Assessment Tool [30].

#### Radiographic assessment

Participants will be required to undergo radiographic imaging of their symptomatic foot (or most symptomatic foot) to grade the presence and severity of first MTPJ OA. Dorso-plantar and lateral radiographic projections will be obtained with the participant weight-bearing in a relaxed bipedal stance position, as described previously [31]. The severity of the osteophytes and the joint-space narrowing at the first MTPJ will be determined using the *La Trobe University radiographic atlas for first MTPJ OA* [31]. All measures will be conducted by two experienced raters ([name], [name]) who were involved in the development of the atlas. The atlas has excellent reliability [31].

### Interventions

#### Random allocation and concealment

Participants will be allocated to the intervention or control groups using minimisation [32] incorporating stratifications by age (18 to 40, 41 to 60, older than 61 years) and sex, using an interactive voice response telephone service provided by the NHMRC Clinical Trials Centre at the University of Sydney, Sydney, Australia.

#### Full-length shoe-stiffening inserts (intervention group)

Participants will be provided with full-length shoe-stiffening inserts at the baseline assessment (a single insert if symptoms are unilateral, or a pair of inserts if symptoms are bilateral). The shoe-stiffening inserts are light (32 to 48 g across the extra small to large size range) and thin (1.5 mm) to allow easy fitting into different types of footwear. The shoe-stiffening inserts are commercially available and are fabricated from prepregnated carbon (Carbon Fibre Spring Plate, Paris Orthotics Ltd., Vancouver, BC, Canada) with the following design characteristics: (1) full length that extends from the heel to the tip of the toes, (2) no arch build-up or contour at the heel and (3) contoured design from proximal to distal to allow for the pitch of the shoe. To maximise comfort and adherence, the inserts will be covered with 3.2-mm PPT® with an Ultralux top layer (PPT2 809 Blue, Langer Biomechanics, Ronkonkoma, NY, USA). A full-length piece of Cambrelle® (Camtex Fabrics Ltd., United Kingdom) will also be applied to the underside of the insert to make it look as similar as possible to the sham insert and to prevent abrasion prematurely wearing the undersurface of the PPT® (Fig. 2). The inserts will be dispensed by the study investigators ([name] or [name]), both registered podiatrists with a minimum 3 years of clinical experience.

**Fig. 2 Fig2:**
[figure not shown]
Shoe insert conditions. Panels **a** to **c** Shoe-stiffening inserts from *side*, *top and bottom view*; Panels **d** to **f** sham inserts from *side*, *top and*
*bottom view*

#### Sham inserts (control group)

Participants allocated to the control group will receive sham inserts (a single insert if symptoms are unilateral, or a pair of inserts if symptoms are bilateral) that will be designed to not affect first MTPJ dorsiflexion but appear as identical to the shoe-stiffening inserts as possible. To achieve this, the shoe-stiffening inserts (i.e. the same as those provided to the intervention group) will be modified by removing the distal end of the insert so that the anterior edge finishes proximal to the level of the MTPJs at the anterior margin of the heel. Similar to the inserts provided to the intervention group, the sham inserts will be sandwiched between a full-length layer of 3.2-mm PPT® with an Ultralux top layer (PPT2 809 Blue, Langer Biomechanics, Ronkonkoma, NY, USA). A full-length piece of Cambrelle® (Camtex Fabrics Ltd., Cumbria, United Kingdom) will also be applied to the underside of the insert (Fig. 2). This sham insert device is necessary in this trial due to participants’ expectation of receiving a ‘take-home’ intervention (i.e. minimises resentful demoralisation). The inserts will be dispensed by [name] or [name].

Mechanical testing of the inserts has been conducted to determine their effect on the bending stiffness of the shoe. A standard Oxford shoe was affixed to a shoe last that was cut at the level of the MTPJs to provide a sagittal-plane axis. The shoe was then dorsiflexed at 5° increments (commencing at 20° of dorsiflexion), and the corresponding force was recorded using a strain gauge. The average moment obtained from an average of five repeated trials was then calculated, as illustrated in Fig. 3. The bending stiffness at 45° of dorsiflexion (the maximum dorsiflexion available with the shoe-stiffening insert placed in the shoe) for each of the conditions was as follows: shoe-only (0.027 Nm/deg), sham insert (0.029 Nm/deg) and shoe-stiffening insert (0.208 Nm/deg). These results confirm that the sham insert has a negligible effect on bending stiffness, whereas the shoe-stiffening insert results in an almost 10-fold increase in bending stiffness.

**Fig. 3 Fig3:**
[figure not shown]
Mechanical testing of the inserts. The measurement of the bending stiffness of the inserts placed inside an Oxford shoe (*upper panel*) and the results of the stiffness of the shoe with and without a sham and full-length shoe-stiffening insert (*lower panel*). The stiffness of each condition is reflected in the gradient of the plots

#### Rehabilitation therapy

Both groups will receive a standardised programme of rehabilitation therapy that is based on a physiotherapy programme for first MTPJ OA reported to be effective in a randomised trial [13]. This will be a home-based programme performed daily for approximately 30 min for 12 weeks, then three times per week for the remaining 40 weeks of the trial. Each therapy session will involve: (1) application of a heat pack for 10 min, followed by (2) self-mobilisation of the first MTPJ for 2 min (distraction and gliding), (3) toe-flexor strengthening exercises (one set of 10 isometric contractions each held for 10 s) and concluding with (4) application of a cold pack (10 min). If the condition is bilateral, both feet will be treated. The programme can be viewed at: https://www.youtube.com/watch?v=cHeO2H6s3K0&feature=youtu.be.

During the baseline assessment, participants will be instructed to perform the exercises by [name] or [name]. Instruction will be given prior to the shoe insert(s) being allocated and dispensed so that [name] and [name] are blinded to intervention allocation. Participants will be provided with all necessary equipment, along with an instruction booklet, so that the exercise programme can be performed unsupervised at home. The rehabilitation therapy will be reviewed at 1 and 12 weeks by research personnel ([name], [name] or [name]), registered podiatrists with at least 19 years’ clinical experience each, blind to intervention allocation. After the 12-week review, participants will be telephoned at monthly intervals to remind them to perform the therapy (to maximise adherence). Rehabilitation therapy has been included as a co-treatment, as using a sham treatment alone may be considered withholding ‘usual’ care.

### Treatment credibility/expectation

A participant’s expectations and their initial beliefs about the credibility of a given intervention may affect the final intervention outcome [33]. Treatment credibility (participants’ beliefs about the logic underpinning the intervention) and treatment expectancy (participants’ perceptions of how much they may benefit) will, therefore, be quantified using the Credibility/Expectancy Questionnaire (CEQ) [34]. The CEQ will be administered after randomisation and allocation. The CEQ consists of six items; three are related to credibility and three are related to expectancy. For each item, participants will be asked to rate the credibility of the intervention and their expectations on a 9-point Likert scale. High scores on the scale indicate that the participant considers the intervention to be credible and expects it to be effective. The CEQ has been shown to have good internal consistency and test-retest reliability [34], and has recently been used to assess the credibility of sham dry needling [35], sham foot orthoses [36], as well as prefabricated foot orthoses and rocker-sole footwear [14] in clinical trials evaluating interventions for foot disorders.

### Outcome measures

Primary and secondary outcome measures will be collected at baseline and at 4, 12, 24 and 52 weeks. These time points have been selected as 4 weeks is considered the earliest time to detect an effect, 12 weeks is considered to be a clinically feasible time point when maximum effect would be expected and is, therefore, the primary endpoint [21, 37], and 24 and 52 weeks will allow us to determine the longer-term effects of the interventions [38]. To minimise participant burden, postal questionnaires will be used for the weeks 4, 24 and 52 assessments. To minimise loss of follow-up data, participants who do not return questionnaires will be reminded up to three times to return their questionnaires.

Biomechanical analyses will be performed at 1 week: this will minimise participant burden during the baseline assessment and enable some level of habituation to the interventions.

#### Primary outcome measure

The primary outcome measure will be the foot pain domain of the Foot Health Status Questionnaire (FHSQ) [39]. The FHSQ consists of 13 questions that assess foot health in four domains: ‘foot pain’, ‘foot function’, ‘footwear’ and ‘general foot health’. There is a total of four questions under the ‘foot pain’ domain. Questions are scored using a Likert response format and the participants’ responses are transformed into a score ranging from 0 to 100 for each domain (0 = worst foot health and 100 = optimal foot health) [39]. The FHSQ has been subjected to an extensive validation process, with each domain being shown to demonstrate high internal consistency (Cronbach’s *α* ≥0.851), good reproducibility (intraclass correlation coefficients (ICCs) ≥0.740) and discriminant validity [39], as well as good responsiveness [40]. Further, the FHSQ is rated as one of the highest-quality foot health status measures currently available [41, 42] and has been used previously in clinical trials of interventions for first MTPJ OA [14, 18, 37].

#### Secondary outcome measures

The secondary outcome measures will include:Foot-related disability (using the foot function domain of the FHSQ) [39]Severity of pain at the first MTPJ whilst walking over a flat surface and during rest over the past week (each via a 100-mm VAS)Self-reported magnitude of symptom change (using a 15-point Likert scale where the responses range from ‘a very great deal better’ to ‘a very great deal worse’). This variable will then be dichotomised into the categories of ‘effective’ (‘a very great deal better’, ‘a great deal better’, ‘a good deal better’, ‘moderately better’) and ‘ineffective’ (‘somewhat better’, ‘a little better’, ‘about the same, hardly any better at all’, ‘no change’, ‘about the same, hardly any worse at all’, ‘a little worse’, ‘somewhat worse’, ‘moderately worse’, ‘a good deal worse’, ‘a great deal worse’, ‘a very great deal worse’) [14]Level of physical activity (using the using the Incidental and Planned Activity Questionnaire (IPAQ)) [43]Health status (using the Short-Form-12 Version 2 (SF-12®) questionnaire [44] and EuroQol (EQ-5D-5L™) questionnaire [45])The use of paracetamol rescue medication (number of participants and mean consumption) and co-interventions to relieve pain at the first MTPJ, documented with a monthly diary throughout the 52-week study period [14, 37, 46]

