### Sample size

The sample size has been determined a priori using SPSS Sample Power 3.0 (IBM Corp., Armonk, NY, USA) based on the FHSQ pain domain as the primary outcome measure. Using a power of 90%, minimal important difference of 12.5 points in the foot pain domain of the FHSQ [37, 54], SD of 16.8 (based on the 12-week time point in our recent trial [14]), assuming a 10% dropout rate, and a significance level set at *α* < 0.05, we estimated that a total of 90 participants will be required.

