### Statistical analysis

Statistical analysis will be performed using the most recent version of SPSS (IBM Corp., Armonk, NY, USA) available at the time of analysis. Analysis will adhere to the intention-to-treat principle for all randomised participants. In participants with bilateral symptoms, the more painful foot will be analysed (or the right foot if they cannot define the more painful foot) to maintain independence of data. Multiple imputation will be used to replace any missing data using five iterations, with sex, age, baseline scores and group allocation as predictors. The exception will be for the following variables where no data substitution will be applied: self-reported magnitude of symptom change, use of co-interventions, and adverse events. Standard tests to assess continuous data for normal distribution will be used and transformation carried out if required. The primary outcome measure will be the foot pain domain of the FHSQ measured at 12 weeks. To avoid over-testing and to minimise the risk of type I error associated with serial measurements, statistical analysis of the effectiveness of the interventions will specifically focus on the change in primary outcome measures between baseline and 12 weeks [55, 56], and differences in the primary and secondary outcome measures between the two groups will be compared at 12 weeks. Continuously scored outcome measures (FHSQ foot pain domain, FHSQ foot function domain, severity of pain at the first MTPJ whilst walking over a flat surface and during rest in the previous week, level of physical activity using the IPAQ, and health status using the SF-12® and EQ-5D-5L™) will be analysed using analysis of covariance with the intervention group and baseline scores entered as independent variables. Self-reported magnitude of symptom change will be compared using relative risk, risk difference and number needed to treat (NNT). Use of paracetamol rescue medication and intervention adherence will be compared using independent groups *t* tests. Use of co-interventions and frequency of adverse events will be compared using relative risk and risk difference statistics. For the biomechanical evaluation, first MTPJ range of motion and maximum first MTPJ dorsiflexion will be compared between groups using analysis of covariance with the intervention group and shoe-only condition scores entered as independent variables.

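### The 15-grade symptom-change rating is compared between arms only as effective/ineffective, which discards information and probably power on this secondary outcome

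*Protocol article*

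**What the plan says.** Under Secondary outcome measures, symptom change is rated "using a 15-point Likert scale where the responses range from" a very great deal better to a very great deal worse. The same item then says: "This variable will then be dichotomised into the categories of" effective and ineffective. Effective holds the four largest improvements, down to 'moderately better'. The other group starts with improvements and runs on through every grade of worsening: "ineffective’ (‘somewhat better’, ‘a little better’, ‘about the same, hardly any better at all’, ‘no change" and so on. The cut cites the group's earlier trial and gives no further reason.

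Under Statistical analysis, the whole comparison is: "Self-reported magnitude of symptom change will be compared using relative risk, risk difference and number needed to treat (NNT"). The rating is not in the list of continuously scored outcomes analysed by ANCOVA, and no ordinal analysis is named. Group differences are to be compared at 12 weeks. Missing ratings are not imputed: "no data substitution will be applied: self-reported magnitude of symptom change, use of co-interventions, and adverse events".

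**The concern.** Of the 15 grades, 4 are effective. The other 11 are 3 grades of smaller improvement, 1 of no change and 7 of worsening. Two kinds of difference between arms therefore become invisible:

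- **Below the cut.** If some participants in one arm move from 'a little better' to 'moderately worse', none of the three statistics changes.
- **Above the cut.** A move from 'moderately better' to 'a very great deal better' also changes nothing. This could matter here because both arms receive a rehabilitation programme that the protocol describes as effective. If many sham participants already reach 'moderately better', part of any added insert benefit would lie among the merged top grades.

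The FHSQ, VAS, activity and health-status scores are analysed on their full scales. The patient's global rating is the graded outcome that is reduced to two classes. If it showed no difference beside a positive FHSQ pain result, a reader could not tell whether the rating truly disagreed or the cut had removed the signal.

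**Working it through.** **1. The plan's own figure.** The only sample-size calculation is for FHSQ pain: "Using a power of 90%, minimal important difference of 12.5 points in the foot pain domain of the FHSQ" and "SD of 16.8 (based on the 12-week time point in our recent trial", with 10% dropout and alpha 0.05. Two-sided testing and 1:1 allocation are assumed, since neither is stated.

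- Standardised effect: 12.5/16.8 = 0.744.
- Normal approximation: n = 2 × (1.960 + 1.282)² / 0.744² ≈ 38 per arm. The t-test version gives 38.95, so 39.
- With dropout: 39/0.9 = 43.3, so 44 per arm and 88 in total, within 2 of the stated 90.

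The stated 90 is reproduced. No power or sample size is given for symptom change.

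**2. Analysable numbers.** Ratings are not imputed, so 90 × 0.9 = 81 remain, about 40 per arm.

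**3. One case in closed form.** Assume a normal latent response shifted by 0.744 SD and a control effective rate of 50%.

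- Insert-arm rate: Φ(0 + 0.744) = 0.772.
- Pooled rate: (0.500 + 0.772)/2 = 0.636.
- SE under no difference: √(2 × 0.636 × 0.364/40) = 0.1076.
- SE under the alternative: √((0.500 × 0.500 + 0.772 × 0.228)/40) = 0.1032.
- Binary power: Φ((0.272 − 1.96 × 0.1076)/0.1032) = Φ(0.59) ≈ 72%.
- A comparison of means on the uncut latent scale with 40 per arm has 91% power.

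The 91% is an upper benchmark, because the actual response has 15 grades. A rank test is the fairer comparator.

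**4. Simulation on 15 grades.** A normal latent response was rounded to grades 1 to 15, with the top four effective. Latent SD was 2, 3 or 4 grades, the control effective rate 20% to 60%, with 4,000 runs per setting. Wilcoxon-Mann-Whitney was compared with a two-proportion z test at two-sided 5%. Ranges are over the control rates and SDs.

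| Shift (SD) | Per arm | Rank power | Binary power | Loss (points) |
|---|---|---|---|---|
| 0.3 | 40 | 24–26% | 16–20% | 4–10 |
| 0.4 | 40 | 37–41% | 25–32% | 7–15 |
| 0.5 | 40 | 53–58% | 38–46% | 11–20 |
| 0.6 | 40 | 68–74% | 51–59% | 13–22 |
| 0.744 | 40 | 83–89% | 67–77% | 12–21 |
| 0.3 | 45 | 26–28% | 18–21% | 6–9 |
| 0.4 | 45 | 40–46% | 30–33% | 9–16 |
| 0.5 | 45 | 59–63% | 43–47% | 14–20 |
| 0.744 | 45 | 89–93% | 74–79% | 12–18 |

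A second simulation, with control rates of 30% to 60% and grade spacings of 0.25 or 0.4 SD, gave losses of 11 to 20 points for shifts of 0.5 to 0.744 SD at 40 per arm.

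**5. A different pattern of benefit.** The uniform shift was then replaced, at 40 per arm.

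- If 35% to 50% of participants improve by 1.5 to 2 SD and the rest do not change, the rank test still has more power.
- If benefit consists only of some participants jumping from below the cut into the effective grades, with everyone else unchanged, the order reverses: binary 68–76%, rank 48–63%. A repeat run gave 67–76% and 46–61%.

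**The case against.** The responder cut is defensible. Every grade is assigned in advance, so there is no data-driven cut-point and no inflation of type I error. It follows the earlier trial and yields a proportion and an NNT that clinicians can use. Graded change is also covered elsewhere: FHSQ pain and function and both VAS scores are analysed on full scales, and new pain is recorded monthly as an adverse event. All of this stands. It supports keeping the responder summary, but it does not support having no comparison of the ordered response.

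The power loss also depends on how benefit arises. Step 5 shows that the sign can reverse, and the protocol's remark that about half of participants in the earlier trial had no change or worsened makes a mixed response plausible. This stands in part: the reversal needs benefit made up solely of jumps across this exact boundary, and mixtures with large individual gains still favoured the rank test.

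A statistical analysis plan, not shown here, might add an ordinal model. It might, but the protocol does not leave the method open: it fixes both the cut and the binary comparison.

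Four stronger readings are tempting and unsupported:

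- **That the cut costs this trial a known amount of power.** The documents give no effect or distribution for this scale, and 0.744 SD is borrowed from FHSQ pain.
- **That improved participants are treated as worsened.** This is true only of those below 'moderately better'.
- **That a planned test is underpowered.** The plan names effect measures for this outcome and no test. The power figures express how well each comparison would separate the arms.
- **That the result would be biased.** Nothing in the documents points to that.

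**Conclusion.** The point holds as a matter of efficiency and information on one secondary outcome. What is lost by construction is certain from the text: all distinctions within the lower eleven grades and within the upper four. The power cost is conditional on an assumed latent shift and about 40 analysed per arm: roughly 11 to 20 points at 0.5 to 0.744 SD (up to 22 on the wider grid) and about 4 to 16 points at 0.3 to 0.4 SD. The primary analysis of FHSQ pain is unaffected. The change is worth making because it is cheap, and an ordinal analysis prespecified before unblinding carries weight that one added afterwards would not.

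**What to change.** In the Statistical analysis section, prespecify an ordinal between-group comparison of the full 15-point response at 12 weeks. Either of these would do:

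- Wilcoxon-Mann-Whitney, reported with the probability that an insert participant gives a better grade than a sham participant.
- Proportional-odds regression with a common odds ratio, with sparse adjacent grades merged blind to allocation.

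Keep the relative risk, risk difference and NNT, with confidence intervals, as the prespecified clinical responder summary, and tabulate all 15 grades by arm.

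The cost is a sentence or two of text and one extra analysis, with no new data or participants. The effect measure is less intuitive than an NNT. With 40/15 ≈ 2.7 participants per grade per arm on average, extreme grades will be sparse and proportional odds hard to check. The rank-based version avoids relying on that model.
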